#### Handling of missing data

If a GP withdraws from the study prematurely, all data collected until that point will be analysed (using the intent-to-treat approach). No additional data will be collected after withdrawing from the study.

#### Data collection

##### EIBI data

After signing an Informed Consent Form (ICF), all GPs in the three municipalities will have access to an e-form embedded in their EHR. This is a clinical data collection form accessible through the EHR, permitting the standardized introduction of screening results from the AUDIT(−C), alcohol-related diagnoses and actions (e.g., the provision of verbal, brief advice/intervention, referral to a digital system for advice or referral to another healthcare provider). At each contact, when they fill in their e-forms, GPs should validate the form and transmit the content in an encrypted format.

Collection of these anonymized patient data will occur via a double secured server to enable safe data transfer and provide a secure environment for data handling and data analysis for research purposes under Belgian legislation [40]. The data protection officer of the KU Leuven will monitor this process.

##### Clinical audit data

For every participating GP, the following data will be collected through a clinical audit of their EHR (Table 1):
The number of patients seen per practice and GP over the past 3 months at 0, 3, 6, 9, 12, 15 and 18 months;The total number of unique patients registered with a GP or practice at 0, 12 and 18 months

GPs send clinical audit data to a double secured server at the Academic Centre for General Practice (ACHG), as authorized in the ICF. The data remain linked to the National Health Services Coding of the consulted GP (NHS-Code).

##### Online GP enquiry

Four times a year, GPs will receive an online questionnaire to (Table 1):
Identify positive and negative experiencesAssess role security and therapeutic commitment of the participating GPs using the Short version of the Alcohol Attitudes Problems Perception Questionnaire (SAAPPQ) [41].Measure views based on TDF domains in relation to knowledge and skills for EIBI, personal priority setting, peer’s views, motivation, readiness for change, and emotional coping.Identify T&S needs.Obtain insights into created opportunities and changes in practice approach (e.g., case findings versus screening, targeted or universal, application of task delegation, waiting room materials, or facilitating internet access).

Every three months, an integrated dataset, linked with NHS-codes, will be created containing:
Absolute number of EIBI per age group, gender, area, and GPClinical audit data of the adult population stratified for gender and age-groups per area and GPGPs characteristics, views, experiences, practice management and needs per area and GPT&S received per GP in the intervention areas

The data will be presented as feedback to the GPs for benchmarking by area in municipality 1 and 2. In order to compare primary and secondary outcome measures, at patient counts per area level, EIBI rates will be grouped per area. Furthermore, a comparison will be made between age groups, gender, and co-morbidity since the start of the study.

## Discussion

The strength of this study is the combination of training and interactive support, tailored to a theory-based implementation strategy (TDF and BCW) and measured during the implementation process. PINO addresses both in- and external barriers and facilitators. This will increase GPs’ experience according to their daily practice and develop good experiences by learning from less successful ones to obtain sustained behavioural and practice change. What also distinguishes PINO from other studies is the inclusion of CAs and evaluating their added value on the delivery of EIBI in general practice.

The PINO-project has some potential limitations. There is a possibility for selection bias within the recruitment of GPs. Highly motivated GPs are more likely to participate compared to more sceptical or less motivated GPs. Nonetheless, a quasi-experimental design is the right fit for this project due to its pragmatic character and the strong external validity [42]. In order to minimize potential bias, necessary precaution was taken when designing the study (e.g., including a control area, using appropriate analytical techniques). Additionally, GPs may address the subject of alcohol consumption but forget to register it in their EHR. It is also possible that GPs remember to register, but do not fill in the e-form correctly. These problems should however occur less in the cities where GPs receive T&S. These concerns have been taken into account while designing this study by integrating both e-forms as well as clinical auditing of the EHR. The e-form provides GPs the opportunity to discuss and systematically record how much alcohol their patients use. Another matter to consider is the possibility that data collection is incomplete due to technical errors, which will be take into account during the analysis.

Nevertheless, the strengths of this study outweigh its limitations. PINO is based on theoretical models of implementation and includes theory-based interventions to promote the desired behaviour. It addresses the attitudes of GPs towards working with at-risk drinkers, and it tailors its program to their views and needs.

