### Outcomes

The primary outcome comprises the overall early identification-rates of GPs during the 18-month period, specified per municipality. This is the proportion of the consulted adult patients (> 18 years) attending general practice for any reason, which were questioned about their alcohol consumption over an 18-months period at area level.

The early identification rates will be measured as follows:
**Numerator:** Patients (> 18 years) attending general practice for any reason who are questioned about their alcohol consumption during the study period of 18 months per area.**Denominator:** Number of unique patients (> 18 years) attending general practice during the 18 months study period per area.

Secondary outcomes will be related to personal views, as measured using the TDF domains, to practice organisation and to provided support. These secondary outcomes comprise (a) the cumulative early identification rates and (b) the cumulative brief intervention rates.

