### Recruitment and eligibility criteria

All GPs within the three municipalities will be addressed systematically through the local GP associations by means of a standard information letter. In addition, a researcher will personally contact the GPs by telephone for clarifying the project and providing reminders. Both GPs and GP trainees will be invited to participate. GPs will be eligible for inclusion if they can read and understand Dutch, and if they work in a general practice within one of the three included municipalities.

GPs sign an ICF specifying their agreement to participate in all trainings, answer the needed online questionnaires and record screening and advise activities in e-forms. E-forms are electronic forms, integrated in the Electronic Health Records (EHR) of GPs. They are developed to record EIBI delivery, diagnosis and referral. There will be no remuneration provided for the work as it is consistent with regular quality practice. All included practices will need to display a poster in the waiting room, indicating their participation in the study. The poster explains that the practice is taking part in a study that evaluates anonymized data from patient records for scientific purposes. Patients may oppose to being included in the study upon simple request.

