**Table 1 Tab1:**
[figure not shown]
SPIRIT flowchart

*CA* community actions, *EIBI* Early Identification and brief interventions, *EHR* electronic health record

Personalisation of the training package will be established by assessing changes in capability, motivation, believes and practice organisations of the participating GPs. Therefore, standardized online inquiries [31] and active interaction during the livestream sessions will be used. The content of each training is based on previously conducted studies on the subject matter [32, 33] and have been piloted in training practices outside the intervention areas. The training sessions will aim to encourage experience-based reflection related to EIBI delivery, GP’s attitudes and highlights practice organisation. During these sessions, skills will be practiced and reflections on how to implement EIBI in relation to practice characteristics will be stimulated. Further, task definition and delegation of possible tasks, management of EHR and other features of practice organization and collaborative care will be emphasized during these training sessions. Importantly, this training package combines theory and practical exercises facilitated by acknowledged and experienced trainers.

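### The protocol expects more complete recording of screening in the T&S areas, and the audit it names as safeguard, as described, counts only patients, so better recording can pass for more screening in the comparison with usual support

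*Protocol article*

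**What the plan says.** All places are in the protocol article.

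- **Outcomes.** The numerator is adult patients "who are questioned about their alcohol consumption during the study period of 18 months per area". No data source is named.
- **Recruitment and eligibility criteria.** In the consent form GPs agree to "record screening and advise activities in e-forms". Of the e-forms it says: "They are developed to record EIBI delivery, diagnosis and referral".
- **EIBI data.** GPs in all three municipalities have the e-form. When they fill it in, "GPs should validate the form and transmit the content in an encrypted format".
- **Training and Support.** Training in municipalities 1 and 2 stresses, among other topics, "management of EHR and other features of practice organization". Individual feedback on EIBI performance every three months goes to those two areas only.
- **Clinical audit data.** Two items are listed. One is "The number of patients seen per practice and GP over the past 3 months", at months 0 to 18. The other is the number of unique patients registered, at months 0, 12 and 18.
- **Discussion.** It admits that GPs may raise alcohol without registering it, or may complete the e-form wrongly. It then says: "These problems should however occur less in the cities where GPs receive T&S". It presents the concern as dealt with in the design by "integrating both e-forms as well as clinical auditing of the EHR".

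**The concern.** A patient enters the numerator if the GP asks and also registers the answer. T&S is meant to change the first step, but through EHR training and performance feedback it can also change the second. The article predicts this and gives the direction: fewer registration failures where T&S is delivered. It offers that as reassurance. For the comparison with municipality 3 it is the reverse, because the outcome would be measured more completely in the arms expected to do better.

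The safeguard does not close the gap. Patients seen and patients registered are denominator-type counts, and an audit limited to them cannot show a consultation in which alcohol was discussed but no e-form was sent. At stake is the reading of the T&S against usual support result. A relative risk above 1 could mean more asking, more recording, or a mixture, and the data described would not separate them. A larger sample would not help, since this is a bias and not imprecision.

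**Working it through.** **1. The plan's own figure.** Sample size estimation expects screening of at least 12%, or a doubling of the assumed current rate; I read this as 6% against 12%. With two-sided alpha 0.05 and 80% power, the two-proportion formula gives 356 per group without continuity correction and 389 with it. The stated 389 is therefore reproduced, which supports that reading. The design effect is 1 + 0.03 × (2256 − 1) = 68.65, and 389 × 68.65 = 26,705 per arm, also as stated. After allowing for clustering, the design thus has an effective 389 patients per arm.

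**2. Model.** Observed rate = true screening rate × recording completeness. Hence

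observed RR = true RR × (completeness under T&S ÷ completeness under usual support).

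With no true effect, the observed RR is the completeness ratio, whatever the true rate.

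**3. Inputs the article does not give.** Completeness by arm is not stated, so the values below are assumptions. The chance of a significant result is taken at n = 389 per arm from the uncorrected two-proportion formula, Φ[(d − 1.96 √(2p̄(1 − p̄)/n)) ÷ √((p₁(1 − p₁) + p₂(1 − p₂))/n)], where d is the difference in observed rates and p̄ their mean. True screening is first set at 12% in both arms.

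| Completeness, usual support vs T&S | Observed rates | Observed RR, no true effect | Chance of significance | True RR if 2.0 is observed |
|---|---|---|---|---|
| 80% vs 90% | 9.6% vs 10.8% | 0.90/0.80 = 1.13 | 8% | 2/1.125 = 1.78 |
| 70% vs 90% | 8.4% vs 10.8% | 0.90/0.70 = 1.29 | 21% | 2/1.286 = 1.56 |
| 60% vs 90% | 7.2% vs 10.8% | 0.90/0.60 = 1.50 | 42% | 2/1.5 = 1.33 |
| 50% vs 100% | 6.0% vs 12.0% | 1.00/0.50 = 2.00 | 83% | 2/2 = 1.00 |

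**4. Sensitivity to the true rate.** The RR column does not change, but the chance of significance does. For 60% against 90% it is 23% at a true rate of 6% (3.6% vs 5.4%), 42% at 12%, and 65% at 20% (12% vs 18%).

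**5. Which comparisons are exposed.** Municipalities 1 and 2 receive the same training and feedback, so their completeness ratio should be near 1. Municipality 3 receives neither, so the contrasts with municipality 3 carry the bias.

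**6. Audit against claim.** The Discussion needs an audit that detects screening missing from the e-forms. The audit section lists two patient counts and no alcohol entry, at month 0 or later. As described, it can neither detect under-registration nor adjust for baseline differences in it.

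**The case against.** The strongest points on the other side are these.

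- **The e-form as sole source is inferred.** No sentence says so, and the section on the integrated dataset gives EIBI counts without a source. This stands as a caveat. Still, no other route to the numerator is described, and EIBI activity for grouping GPs in the booster sessions is measured through e-form use.
- **The printed audit list may be incomplete.** Elsewhere the article mentions audit data by age and gender and a comparison by co-morbidity, and Table 1 is not shown. A reader might infer that the audit certainly holds nothing on screening. The document does not support that. It supports the narrower statement that the audit as described cannot detect unregistered screening.
- **Municipality 3 is not left without means to record.** Its GPs have the e-form, agree to use it, receive practice tools, and according to the abstract get a minimal intervention intended to facilitate data collection. This may narrow the gap. It does not equalise EHR training or feedback, and the Discussion still expects a difference.
- **The largest scenario is extreme.** It assumes perfect recording in one arm, half in the other, and a true usual-support rate of 12%, twice the 6% implied by the sample size section. That is fair; the milder rows are shown for this reason.
- **The limitation is disclosed.** Under-recording is. What is wrong is that the differential is treated as reassuring and that an audit is credited with a check it does not, as described, perform.

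**Conclusion.** The point holds for T&S against usual support. By the article's own expectation recording will be more complete in municipalities 1 and 2, and nothing described separates recording from screening. The size cannot be determined from the document. Over the assumed completeness range, recording alone gives a relative risk from 1.13 to 2.0, the latter equal to the whole planned effect. This rests on the e-form being the numerator source and on the audit being as listed.

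Two stronger conclusions are tempting and not supported. One is that a positive result would be wholly an artefact: without completeness figures nobody can say so, and with a modest gap (80% against 90%) most of an observed doubling would be real. The other is that the trial cannot answer its question about community actions: municipalities 1 and 2 share the same T&S, so that comparison is much less affected.

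**What to change.** 1. **Equalise recording instruction.** Give GPs in municipality 3 the same technical e-form instruction and registration reminders as the T&S areas, without the screening training. This addresses the cause. The cost is an instruction sheet and reminders; the downside is that it may slightly raise recording, or screening itself, in the usual-support area.
2. **Add one count to the existing audit query.** In all three areas and at every audit including month 0, collect the number of unique adults with a structured alcohol entry in the EHR (AUDIT(-C), units per week, or an alcohol code). Report a numerator of e-form or EHR entry as a supporting sensitivity analysis. It reduces the bias but does not remove it: questioning recorded nowhere, or only in free text, is still missed, and T&S may improve EHR entries too. Agreement between the two numerators is therefore not proof of a screening effect. The cost is one extra field, plus a check that the consent form, which authorises the audit transfer, covers it.
3. **Correct the Discussion.** Remove the claim that the current audit addresses under-registration, present the expected difference between areas as a bias favouring T&S, and state that the T&S against usual-support effect is an effect on recorded screening. This costs only wording.

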## Data Availability

The research team will have access to interim results and the final data set. Every three months, the AB Inbev Foundation will receive aggregated interim results. The study results will be disseminated via open-access, peer-reviewed publications and conference presentations. Study materials are available on request. This protocol is written according to the SPIRIT guidelines for clinical trial protocols [43].

## Abbreviations

ACHG: Academic Centre for General Practice
AUDIT: Alcohol Use Disorder Identification Test
AUDIT-C: Alcohol Use Disorder Identification Test - Consumption
BCW: Behavioural Change Wheel
BI: Brief Intervention
CA: Community Action
DPO: Data Protection Officer
EC: Ethics Committee
EHR: Electronic health record
EIBI: Early Identification and Brief Intervention
GP: General Practitioner
NHS: National Health Service
SARS-CoV 2: Severe Acute Respiratory Syndrome Corona Virus 2
T&S: Training and Support
TDF: Theoretical Domains Framework
